## Abstract

**Background:**

Hypertension is the most prevalent chronic condition and a significant risk factor for cardiovascular and kidney diseases. The efficacy of health behavioral interventions in blood pressure (BP) control has been demonstrated by a large and expanding body of literature, with “adherence” playing a crucial role. WeChat is the most common social communication mobile app in China, and it has been shown to be an acceptable delivery platform for delivering health interventions. The WeChat-based health behavioral digital intervention program (WHBDIP) showed high feasibility and efficacy. However, the results regarding BP improvement between the WHBDIP and control groups were inconsistent.

**Objective:**

The objective of this study is to develop a WHBDIP and assess its efficacy in controlling BP and improving adherence among patients with hypertension.

**Methods:**

A 2-arm, parallel-group, and randomized trial design was used. Patients older than 60 years and with hypertension were randomly assigned to either the control group or the experimental group, which received a 12-week intervention. The program, primarily developed based on the Behavior Change Wheel (BCW) theory, offers health education on exercise, diet, BP monitoring, and medicine adherence (MA). It also includes other behavior interventions guided by an intervention manual, incorporating behavior change techniques (BCTs). The primary outcomes encompass BP and adherence indicators, while the secondary outcomes encompass cardiovascular function indicators, body composition indicators, learning performance, satisfaction, and acceptability. The exercise and blood pressure monitoring adherence (BPMA) indicators for the WHBDIP group were assessed weekly via WeChat during the initial 3 months, while other outcome data for both groups will be collected at the baseline assessment phase, 3 months after the intervention, and 1 year after the program.

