### Sample Size

The sample size was calculated based on the primary outcome of BP. The effect size, widely used to measure treatment effects of continuous outcomes, is calculated as the difference between groups divided by the pooled SD. A previous meta-analysis, comparing mHealth intervention treatments with other traditional treatments, with the primary outcome being BP, reported an effect size of 0.7 [17]. Assuming α=.05, β=.2, and accounting for up to 20% attrition, a sample size of 68 is needed for this study.

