### Randomization, Allocation, and Blinding

This study followed a process of randomization. Before randomization, an individual not involved in subject recruitment and data collection used the SPSS software (version 23; IBM Corp) to generate 68 random numbers and assigned them to either 1 (experimental group) or 2 (control group) using visual binning. These 68 sets of random numbers were printed separately and sealed in individual envelopes. After recruiting a participant, the facilitator opened the envelopes sequentially, and the number found inside each envelope determined the group to which the particular participant belonged. In this study, we blinded data collectors both before and after the trial.

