### Outcomes

#### Primary Outcomes

BP will be measured using a cardiovascular function monitor (BX-CFTI-100, Institute of Intelligent Machines) at 3 time points: the first baseline assessment phase (T0), the 12-week end point assessments phase (T1), and the end of the 1-year program (T2). The assessment details have been published elsewhere [32].

Exercise adherence (EA), DA, MA, and BPMA indicators were collected once a week through WeChat for the intervention group until T1. The BPMA will also be collected at T0, T1, and T2 for the control group. The exercise adherence indicator was calculated as the ratio of actual exercise time that meets the prescription's recommended intensity to the total time of the prescription-recommended intensity. PAT will be measured as an indicator by questioning subjects in both groups at T0, T1, and T2 about the type, duration (in minutes), and frequency (per week). It will be measured using the minutes or metabolic equivalent per week. The MA indicator will be measured at T0, T1, and T2 for both groups using the Modified Morisky Scale (Chinese version-MMS-8, Certificate Number: 8538-1877-1559-6025-5310) [34-36], which includes 8 simple questions. The rating is “poor medication adherence” for a final total score of <6 points, “moderate medication adherence” for a score of 6-7, and “good medication adherence” for a score of 8. Dietary adherence (DA) will be assessed at T1 and T2 for both groups based on their compliance with the “types of diet” and the “recommended amount of diet” (3 response levels for each question).

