### Statistical Analysis

All analyses will be performed using SPSS. Continuous variables will be presented as mean and SD values. Categorical variables will be expressed as numbers and percentages. Independent samples *t* tests and chi-square tests will be conducted to assess the significance of differences in baseline characteristics or outcomes between the control group and intervention group at 3 time points: before the start of the intervention, 12 weeks after the intervention, and 1 year after the program. Paired *t* tests and McNemar's test will be used to compare the differences in some outcomes before and after the 3-month intervention, as well as before the trial and after the end of the program. A *P* value of less than .05 will be considered statistically significant.

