## Results

The study was funded in December 2021. The WHBDIP trial was approved by the Ethics Committee of Bengbu Medical College in June 2022 (2022-103) and registered in August 2022 (ChiCTR2200062643). Patient recruitment for those with hypertension started on September 5, 2022, and was completed on September 19, 2022. The 3-month intervention and phased data collection were completed in January 2023. Data analysis will commence in August 2023, and the final 1-year health outcome results will be collected in September 2023. We expect the primary outcomes to show changes in adherence indicators during the 3-month intervention, and health outcomes, including BP and other cardiovascular indicators, to change after the intervention and 1 year later. Furthermore, we will report on dropout rates and reasons for dropout during the trial.

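### BP and several adherence indicators are all primary, at two visits and at P<.05 each, with no lead outcome named, although the trial is sized on BP alone

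*Protocol article*

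**What the plan says.** - **Primary outcomes.** The abstract states: "The primary outcomes encompass BP and adherence indicators". The Primary Outcomes section covers BP, exercise adherence (EA), physical activity time (PAT), medicine adherence (MA), dietary adherence (DA) and BP monitoring adherence (BPMA). None is ranked above the others.
- **Visits.** BP, PAT and MA are measured in both arms at T0, T1 and T2, and DA in both arms at T1 and T2. EA is described for the intervention arm only, weekly until T1. BPMA is collected weekly until T1 in the intervention arm, and at T0, T1 and T2 in the control arm.
- **Tests.** The Statistical Analysis section plans t tests and chi-square tests between arms at baseline, 12 weeks and 1 year, plus paired before-after tests. Its one decision rule is that a P "value of less than .05 will be considered statistically significant".
- **Sample size.** "The sample size was calculated based on the primary outcome of BP". No BP measure and no visit is given.
- **Timing.** The Results section puts completion of the 3-month data in January 2023, and continues: "Data analysis will commence in August 2023, and the final 1-year health outcome results will be collected in September 2023".

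**The concern.** The article does not agree with itself on what the primary outcome is. The Sample Size section treats BP as the outcome that drives the design, while the abstract and the Primary Outcomes section give BP and the adherence indicators equal standing. Each is tested at two follow-up visits against the same .05 threshold.

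With no lead outcome, lead visit or order of testing, a significant result on any listed outcome at either visit could be presented as a positive primary result. The .05 threshold would then limit the error of each test but not the error of the trial's main claim. The planned dates add to this. An analysis that starts in August 2023 precedes the 1-year data, so T1 results could be known while the deciding measure and visit are still open.

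**Working it through.** **1. The plan's own figure.** Inputs from the Sample Size section: "reported an effect size of 0.7", and "Assuming α=.05, β=.2, and accounting for up to 20% attrition, a sample size of 68 is needed for this study". Per arm, n = 2(z_alpha + z_beta)²/d².

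- One-sided: 2(1.645 + 0.842)²/0.49 = 25.2, so 26 per arm. With attrition, 26/0.8 = 32.5, so 33 per arm and 66 in total.
- Two-sided: 2(1.960 + 0.842)²/0.49 = 32.04, so 33 per arm (34 by the exact t test). That is 66 or 68 in total before any attrition.

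The stated 68 is therefore recovered for one comparison on one outcome: within 2 one-sided with attrition, or exactly two-sided without it. Neither route leaves room for several primary tests.

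**2. Count of between-arm primary tests.** EA is excluded because it has no control-arm measurement. The paired tests are not counted.

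| How counted | T1 | T2 | Total |
|---|---|---|---|
| BP once; BPMA not compared at T2 | 5 | 4 | 9 |
| BP once; BPMA compared at both | 5 | 5 | 10 |
| SBP and DBP separate; BPMA not compared at T2 | 6 | 5 | 11 |
| SBP and DBP separate; BPMA compared at both | 6 | 6 | 12 |

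**3. Chance of at least one false positive among k tests at .05, with no true effect on any of them.**

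Independent tests: 1 − 0.95^k.

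- k = 9: 1 − 0.630 = 37.0%
- k = 12: 1 − 0.540 = 46.0%
- T1 alone: k = 5 gives 22.6%, k = 6 gives 26.5%

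Common correlation ρ between two-sided z tests: 1 − ∫[Φ((1.96 − √ρ z)/√(1−ρ)) − Φ((−1.96 − √ρ z)/√(1−ρ))]^k φ(z) dz.

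| k | ρ = 0.3 | ρ = 0.5 | ρ = 0.7 |
|---|---|---|---|
| 5 (T1 only) | 20.9% | 18.3% | 14.8% |
| 6 (T1 only) | 24.1% | 20.7% | 16.4% |
| 9 | 32.6% | 26.9% | 20.2% |
| 12 | 39.7% | 31.9% | 23.2% |

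The article gives no correlations, so these values of ρ are assumptions.

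**4. Could all tests stay equal and simply be corrected?** With Bonferroni over 12 tests, alpha = .05/12 = .00417. The two-sided t test at d = 0.7 then has 47% power with 34 per arm (68/2, assuming equal arms) and 35% with 27 per arm (34 × 0.8 = 27.2). Reaching 80% would need 59 per arm, and 59/0.8 = 73.75 gives 74 per arm or 148 in total. Recruitment closed in September 2022, so this route is not open without a serious loss of power.

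**The case against.** The strongest reply is that the article sets a significance threshold and not a rule for trial success. Its objective joins BP control and better adherence. If both were required, the false-success rate would not inflate in this way. This stands: the percentages above hold only under an any-one-suffices reading, which the article neither adopts nor rules out.

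The second reply is about the count, and it also stands. Twelve is an upper figure, since BP is listed as one outcome and BPMA at T2 is not described for the intervention arm. The Results section also links adherence changes to the 3-month period and BP changes to both the end of the intervention and 1 year, which suggests a narrower set of comparisons.

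Third, test ordering is often left to an analysis plan, and the trial was registered in August 2022, before recruitment. A hierarchy may exist in a document not shown. Sizing on one primary is not itself an error, and the Sample Size wording can be read as marking BP as the lead. This stands in part. It does not remove the conflict between one primary in that section and several elsewhere, nor does it supply the missing BP measure and visit.

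Two stronger readings are tempting. A reader might infer that the trial has a 46% false-positive rate, but that figure needs 12 tests, independence and an assumed success rule together. A reader might also infer from the dates that the primary will be picked after results are seen. The dates make that possible, and nothing in the article shows that it happened or is intended.

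**Conclusion.** The point holds in a limited form. The published plan names several equal primary outcomes, compares the arms on them at two visits with one uniform threshold, and sizes the trial on an unspecified BP measure. As written, it does not control the chance of a false primary claim.

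Under an any-one-suffices reading with 9 to 12 tests, that chance is about seven to nine times the nominal 5% if the tests are independent, and about four times at a correlation of 0.7. At T1 alone it is about three to five times. The result rests on the assumed success rule, the assumed correlations and the stated range for the count. The direction holds under every count tried; the exact size cannot be known from the article.

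**What to change.** - Before the August 2023 analysis, name one BP measure at one visit as the single lead primary, tested at two-sided .05. This matches the Sample Size section. Baseline-adjusted SBP at T1 is one suitable example, not the only one.
- Place the other BP measure, the other visit and the adherence indicators in a pre-specified fixed order, or test them with Holm correction. They may be lower-ranked primaries or key secondaries; demoting adherence altogether is not required, given the stated objective.
- State whether BPMA is compared between arms at T2, and that EA is descriptive for the intervention arm.
- Date the change in the analysis plan and the registry, and disclose that T1 data had already been collected by January 2023.

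No new data or participants are needed. The costs are an openly declared change to the primary outcomes after T1 collection, and that adherence alone could no longer be claimed as an unadjusted primary success.

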**Results:**

The trial will assess the efficacy of WHBDIP for patients with hypertension (N=68). The WHBDIP seeks to enhance participants' knowledge of healthy behaviors and assist patients in developing positive health behaviors to improve their health outcomes. Patient recruitment for individuals with hypertension commenced on September 5, 2022, and concluded on September 19, 2022. The 3-month intervention and phased data collection were finalized in January 2023. Data analysis will commence in August 2023, and the final 1-year health outcome results will be collected in September 2023.

**Conclusions:**

A successful WHBDIP will establish the management mode as a feasible approach for hypertension management in the community. Additionally, it will pave the way for the development of related mobile health programs.

**Trial Registration:**

Chinese Clinical Trial Registry ChiCTR2200062643; https://tinyurl.com/mwyv67wk

**International Registered Report Identifier (IRRID):**

PRR1-10.2196/46883

## Introduction

Hypertension, the most prevalent chronic condition and a significant risk factor for stroke, ischemic heart disease, and kidney disease, has become a primary contributor to the global disease burden [1,2]. It is directly responsible for more than 8.5 million deaths worldwide annually [3]. Furthermore, it imposes a substantial economic burden. In China, hypertension accounts for 6.6% of the total national health expenditure [4]. Over the past 30 years, the number of adults with hypertension has risen from 650 million to 1.28 billion [1]. In China, the prevalence of hypertension in adults was 25.2% [5] with awareness, treatment, and control rates at 51.5%, 45.8%, and 16.8%, respectively [6].

Less than half of young patients with hypertension and two-thirds of eligible older patients with hypertension achieve blood pressure (BP) control goals [6]. The low control rate may be attributed to lifestyle-related risk factors, such as poor eating habits and low levels of physical activity [2]. Researchers have found that encouraging patients to follow the recommended health behaviors significantly reduces BP. For example, patients under the supervision of medication taking experienced a 5-mm Hg decrease in daily systolic blood pressure (SBP) compared to unsupervised individuals [7]. Adhering to the Dietary Approaches to Stop Hypertension (DASH) resulted in a 26% reduction in developing high BP [8], and in those already diagnosed with hypertension, SBP and diastolic blood pressure (DBP) decreased by 1.5 and 1.1 mm Hg, respectively [9]. Following various types of recommended exercise led to an SBP reduction of 7.23-8.69 mm Hg [10]. Improving BP monitoring adherence behavior resulted in SBP and DBP reductions of 2.53-4.2 and 1.45-2.4 mm Hg, respectively [11]. High medication adherence, combined with comprehensive interventions such as diet and exercise management, can achieve better BP control effects [12,13]. The results showed a reduction of 12.1 and 26.1 mm Hg in SBP and DBP, respectively, before and after comprehensive health behavior intervention [14], and a decline of 7.5 and 3.9 mm Hg for SBP and DBP, when compared with nonintegrated intervention group [15]. Considering all of this evidence, it appears that comprehensive health behavior intervention can achieve better BP control effects, with adherence being the key.

Digital health (such as mobile health [mHealth] or telehealth) intervention strategies have been used to improve hypertension management outside the hospital. These strategies enhance patient adherence behaviors and increase the feasibility of delivering convenient, continued health interventions in primary health care settings with unequal resource distribution and understaffing. Several recent meta-analyses have demonstrated that using an internet-based interactive intervention mode combining health information with decision support via a computer or mobile phone could lead to a reduction of mean SBP by 2.23-3.74 mm Hg and mean DBP by 1.14-2.99 mm Hg [16-18]. Most of the interventions conducted by the investigators aimed to influence “self-management” or “adherence behaviors” in patients with hypertension [16-18]. Another systematic review of the literature showed the improvement of patient adherence after mHealth intervention [12,17,19-21].

WeChat, a mobile app, is the most prevalent social communication tool in China, with over 1 billion monthly active users of all ages. Approximately 902 million users log into WeChat every day [22]. A substantial amount of prior research in health promotion has focused on WeChat-based programs, which have demonstrated high acceptability, feasibility, and efficacy [23]. WeChat-based health interventions have been found to increase adherence and willingness to seek treatment, improve follow-up rates, enhance health outcomes, quality of life, and self-care ability, and also promote patient satisfaction [23-28]. For hypertension management, WeChat-based programs showed improvements in BP monitoring, diet, self-efficacy, and self-management scores [29,30]. However, the effect of lowering BP is inconsistent. One study reported a significant improvement in BP (SBP: –6.9 and DBP: –3.1 mm Hg) between the intervention and control groups [30], while another study showed no statistical differences between the 2 groups [31]. Therefore, we aim to assess the effectiveness of the WeChat-based health behavioral digital intervention program (WHBDIP) in 2 groups after 3 months of intervention and at the end of an extended additional 7 months. This program involves exercise, diet, BP monitoring, and medication adherence intervention strategies. Our plan is to investigate whether this approach is accessible and effective in improving outcomes for older individuals with hypertension.

## Methods

### Trial Design and Setting

This is a 2-arm, parallel-group, randomized trial that includes a WeChat-based health behavioral digital intervention lasting for 12 weeks. The trial has been conducted at 2 community health centers, both located in Anhui province—1 in Hefei and the other in Bengbu. The primary data collection and evaluation will take place at 3 time points: the beginning of the project, after 3 months of intervention, and 1 year after the project starts.

### Patients

In this trial, patients with hypertension were recruited through phone or verbal invitations from community health centers. Interested individuals were asked for further information by contact staff members. To promote recruitment, relevant physical health assessments were offered for free to candidates, and unqualified candidates were excluded at this stage. Written informed consents were obtained from eligible patients before randomization. The inclusion criteria for the participants were as follows: (1) previous diagnosis of essential hypertension by medical institutions or initiation of antihypertensive drug treatment, (2) older than 60 years of age, and (3) proficiency in using smartphones and the WeChat app. Patients with the following conditions were excluded: (1) prehypertension or not taking antihypertensive drugs; (2) contraindications to exercise, such as serious cardiovascular and cerebrovascular diseases, muscle and joint pain, or inability to participate in exercise as recommended by a doctor; (3) diabetes or nephrosis; (4) participation in other health intervention programs; and (5) not having a sphygmomanometer.

### Sample Size

The sample size was calculated based on the primary outcome of BP. The effect size, widely used to measure treatment effects of continuous outcomes, is calculated as the difference between groups divided by the pooled SD. A previous meta-analysis, comparing mHealth intervention treatments with other traditional treatments, with the primary outcome being BP, reported an effect size of 0.7 [17]. Assuming α=.05, β=.2, and accounting for up to 20% attrition, a sample size of 68 is needed for this study.

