## Discussion

The WHBDIP is a WeChat-based digital health program that aims to improve the self-management of BP and promote adherence behavior change among patients with hypertension. If the effectiveness of WHBDIP can be verified, it may be attributed to several key characteristics. First, all interventions were developed based on robust evidence, and we further optimized them. Similar to DASH, a proven effective diet for patients with hypertension, we have created a map of food portions tailored to the dietary characteristics of Chinese people and included beverage options in the scoring table. Second, WHBDIP is a theory-based intervention tailored to patients with hypertension. We specified the target behavior (adherence) and conducted a scientific and systematic procedure to identify the appropriate functions from the 9 behavior functions. We then selected the corresponding BCTs from Michie et al’s [33] taxonomy based on the BCW. These BCTs were compiled into the intervention manual, which will serve as the foundation for the development of the mHealth intervention program. Third, we provided tailored interventions, including intelligent personalized exercise prescriptions and different intervention contents for adherence. For example, people with different movement barriers require different persuasion techniques. Fourth, we provided one-to-one web-based health services, which could increase participant satisfaction. Fifth, this trial involved health-related professionals and followed a community-based telehealth intervention approach. Finally, we designed this trial to meet methodological demands, including adequate power, allocation concealment, and necessary blinding.

If the WHBDIP is proven to be effective, it could be integrated into the upcoming eHealth promotion program. We will develop community-based apps to promote the management of patients with hypertension, including patient terminals and health service provider terminals. The app will deliver personalized e-interventions, such as reminders, videos, and other content, to patients through specific logic that incorporates behavioral change techniques. This will enable the manual intervention to be automated. It may serve as an alternative, convenient, and cost-effective approach, deserving further experimental verification, for doctors and nurses in primary health care institutions to provide tailored and consistent health services for patients with hypertension.

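### The planning effect size of 0.7 is not reconciled with the 2.23-3.74 mm Hg SBP reduction cited from a reference group that includes its source, so "adequate power" holds only for large BP effects

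*Protocol article*

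**What the plan says.** Sample Size states: "The sample size was calculated based on the primary outcome of BP". It does not say whether this is systolic or diastolic pressure. It defines the effect size as a quantity that "is calculated as the difference between groups divided by the pooled SD", and takes its value from a meta-analysis of mHealth against traditional treatment that, "with the primary outcome being BP, reported an effect size of 0.7 [17"]. The remaining inputs are "Assuming α=.05, β=.2, and accounting for up to 20% attrition", and the result is 68 patients. No difference in mm Hg and no SD is given.

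The Introduction says of internet-based interactive interventions that they "could lead to a reduction of mean SBP by 2.23-3.74 mm Hg and mean DBP by 1.14-2.99 mm Hg [16-18"]. It also quotes larger effects: 6.9 mm Hg SBP and 3.1 mm Hg DBP in one WeChat study, set beside a second WeChat study with no difference, and 7.5 and 3.9 mm Hg for a comprehensive intervention against a nonintegrated one.

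Statistical Analysis compares the arms with independent-samples t tests at each time point, where a P "value of less than .05 will be considered statistically significant". The Discussion lists the design's strengths as "including adequate power, allocation concealment, and necessary blinding".

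**The concern.** Reference 17 supports a large standardised effect in one section and, as one of three sources, a small raw effect in another. The link between them is the SD, which the article does not state. If the SD is of ordinary size for patients' SBP, the trial has 80% power only for differences well above those the article cites from references 16-18.

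What is at stake is how a non-significant BP result will be read. In a trial described as adequately powered, such a result invites the conclusion that the programme does not lower BP, although a reduction of 2-4 mm Hg would usually have been missed.

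**Working it through.** **1. The plan's own figure.** Inputs from Sample Size: d = 0.7, α = .05, power 80%. Two-sided testing is assumed because sidedness is not stated, and 1:1 allocation (34 per arm) is assumed.

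- Normal approximation: n = 2 × (1.96 + 0.84)² / 0.7² = 32.0, so 33 per arm.
- t test: 33.02, so 34 per arm and 68 in total.

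So 68 is the two-sided t-test figure before any allowance for attrition; with 20% loss it would be 34/0.8 = 42.5, so 43 per arm or 86. One-sided testing gives 26 per arm, or 33 per arm (66) after inflation, which is near 68 but not equal to it. This is a separate matter. It is used here only to justify showing both 34 per arm (all analysed) and 34 × 0.8 = 27 per arm (after 20% loss).

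**2. SD needed for d = 0.7.** By the article's definition, SD = difference / 0.7.

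| Quoted effect (Introduction) | SBP: SD needed (mm Hg) | DBP: SD needed (mm Hg) |
|---|---|---|
| References 16-18, lower end | 2.23/0.7 = 3.2 | 1.14/0.7 = 1.6 |
| References 16-18, upper end | 3.74/0.7 = 5.3 | 2.99/0.7 = 4.3 |
| One WeChat study | 6.9/0.7 = 9.9 | 3.1/0.7 = 4.4 |
| Comprehensive intervention | 7.5/0.7 = 10.7 | 3.9/0.7 = 5.6 |

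This step uses only figures in the article.

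**3. Power for each quoted SBP effect.** The SD is an assumption, with a range of 8-20 mm Hg. Power is from the noncentral t distribution with d = difference/SD, noncentrality d × √(n/2) and 2n − 2 degrees of freedom, two-sided α = .05. Each cell gives power at 34 / 27 per arm.

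| SBP difference | SD 8 | SD 10 | SD 15 | SD 20 |
|---|---|---|---|---|
| 2.23 | 21% / 17% | 15% / 13% | 9% / 8% | 7% / 7% |
| 3.74 | 48% / 39% | 33% / 27% | 17% / 15% | 12% / 10% |
| 6.9 | 94% / 88% | 80% / 70% | 46% / 38% | 29% / 24% |
| 7.5 | 97% / 92% | 86% / 77% | 53% / 44% | 33% / 27% |

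The most favourable cell for the 2.23-3.74 range is 3.74 mm Hg at SD 8 (d = 0.47). One-sided testing would raise it from 48% to 60% at 34 per arm, still short of 80%.

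**4. Difference detectable with 80% power.** This is 0.69 SD at 34 per arm and 0.78 SD at 27 per arm. At SD 10 that is 6.9 and 7.8 mm Hg; at SD 15 it is 10.3 and 11.7 mm Hg.

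**The case against.** The strongest reply is that 2.23-3.74 mm Hg is the wrong comparator. That range describes internet-based interactive interventions in general, whereas the article presents its programme as a comprehensive one. For a comprehensive intervention the Introduction quotes 7.5 mm Hg, and for one WeChat study 6.9 mm Hg. At SD 10 these have 86% and 80% power with 34 per arm, so 0.7 is not out of reach. This stands in part. It depends on an SD near 10: at SD 15 the same effects have 53% and 46% power. Nor does Sample Size rest 0.7 on those studies; it attributes the figure to reference 17. The Introduction itself calls the BP effect of WeChat programmes inconsistent. If DBP was the sized component, even those studies need an SD of only 4.4-5.6 mm Hg.

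Three stronger readings are tempting, and the article supports none of them.

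- A reader might infer that 0.7 and 2.23-3.74 mm Hg contradict each other outright. They do not without an SD, and the article gives none. The gap is a conclusion over an assumed SD range.
- A reader might infer that 2.23-3.74 mm Hg is the effect the investigators expect. No section names it as the target.
- A reader might infer that 0.7 is misattributed. The Introduction pools three meta-analyses and does not say which figure comes from reference 17, so this cannot be judged from the article. Checking the figure is a fair request; demanding its removal is not.

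It can also be said that interpretation of null results belongs in the analysis plan. However, the article itself publishes both the power justification and the adequacy claim, so qualifying them belongs there too.

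**Conclusion.** The concern holds as a failure to reconcile, not as an arithmetical error. The article's standardised effect and the raw effects it cites from an overlapping set of sources agree only at an SBP SD of 3.2-5.3 mm Hg. At any assumed SD from 8 to 20 mm Hg, power for 2.23-3.74 mm Hg is below 50%. For 6.9-7.5 mm Hg it reaches 80% only if the SD is about 10-11 or smaller and all 68 patients are analysed. The adequacy claim in the Discussion is therefore true only for large BP effects.

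This rests on the assumed SD range, two-sided testing, equal arms, and the unadjusted t test that the article names. The power figures would shift if the observed SD fell outside the range, which the baseline data can settle.

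**What to change.** 1. In Sample Size, state whether SBP or DBP was sized, and give the mm Hg difference and SD behind 0.7. Check 0.7 against reference 17 and explain how it relates to the range in the Introduction.
2. Compute the BP SD from the baseline (T0) data, pooled without reference to arm. With it, report the detectable difference (about 0.69 SD at 34 per arm, 0.78 SD at 27 per arm) and the power at 2.23, 3.74, 6.9 and 7.5 mm Hg SBP.
3. In the Discussion, replace the general claim of adequate power with one limited to effects of the detectable size.
4. Report the between-group BP difference with its 95% CI, so that a non-significant result is not read as excluding the smaller effects the article cites.

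The cost is wording and one SD calculation from data already collected. Recruitment closed in September 2022, and no extra patients are asked for. The downside is that the stated power becomes less favourable.

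### The planned 68 patients are what the design needs with no dropout; at the 20% attrition the protocol says is covered, two-sided power is about 71%, not 80%

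*Protocol article*

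**What the plan says.** The Sample Size section of the protocol article bases the calculation on blood pressure. It defines the effect size as a quantity that "is calculated as the difference between groups divided by the pooled SD" and takes its value from an earlier meta-analysis of mHealth interventions, which, "with the primary outcome being BP, reported an effect size of 0.7". The conclusion is: "Assuming α=.05, β=.2, and accounting for up to 20% attrition, a sample size of 68 is needed for this study".

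Nothing is added to that figure elsewhere. Under Randomization, Allocation, and Blinding, the allocation list was made by using software to "generate 68 random numbers and assigned them to either 1 (experimental group) or 2 (control group) using visual binning", and the Abstract gives N=68.

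The Statistical Analysis section plans independent-samples t tests for differences between groups, where a P "value of less than .05 will be considered statistically significant". It names no direction and no one-sided test. The Discussion then says that "we designed this trial to meet methodological demands, including adequate power, allocation concealment, and necessary blinding".

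**The concern.** A total of 68 is small for a standardised effect of 0.7 at 80% power if one patient in five may be lost. It looks like the number of patients who must be analysed, with no inflation for loss.

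If so, the trial lacks the stated power at the stated attrition, and the Discussion's power claim has no support. This bears on how the result is read. The Introduction says earlier WeChat programmes gave inconsistent blood pressure results, so a non-significant result is plausible. Readers would take it as coming from a trial that kept 80% power after dropout, and would give it more weight than it deserves. Follow-up runs to one year, and the Results section promises to report dropout, so loss is a practical matter here.

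**Working it through.** **Inputs**

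- Standardised difference d = 0.7 (Sample Size).
- α = .05, β = .2, so power 80% (Sample Size).
- Attrition up to 20% (Sample Size).
- Test: independent-samples t test at P < .05 (Statistical Analysis).
- Allocation 1:1, assumed. The document gives 68 numbers split into two groups but no ratio.
- Two-sided test, assumed. The document does not state sidedness.

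**Formula.** With n analysed per arm, the degrees of freedom are 2n − 2 and the noncentrality is δ = d·√(n/2). Two-sided power is the probability that a noncentral t variable with noncentrality δ falls outside ±t(0.975, 2n − 2).

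**Step 1: reproduce 68.**

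- n = 33: δ = 0.7·√16.5 = 2.843, critical value 1.998, power 79.97%.
- n = 34: δ = 0.7·√17 = 2.886, critical value 1.997, power 81.2%.

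The smallest n reaching 80% is 34 per arm, and 2 × 34 = 68. The protocol's figure is reproduced exactly, with no patient lost. The normal approximation, 2·((1.960 + 0.842)/0.7)² = 32.04, rounds up to 33 per arm, or 66, also before attrition.

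**Step 2: apply the 20% allowance.**

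| Method (two-sided) | Before attrition | n/(1 − 0.2) | n × 1.2 shortcut |
|---|---|---|---|
| Noncentral t | 68 | 85 (86 with equal arms) | 82 |
| Normal approximation | 66 | 83 (84 with equal arms) | 80 |

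Every two-sided route that includes attrition gives between 80 and 86.

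**Step 3: power if 68 are randomised and 20% are lost.** 68 × 0.8 = 54.4, so about 54 patients, 27 per arm. Then δ = 0.7·√13.5 = 2.572, the critical value is 2.007, and power is 71.4% (73.0% by the normal approximation). The type II error is 1 − 0.714 = 0.286.

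**Step 4: effect detectable with 80% power.** Solving for d gives 0.690 at 34 per arm and 0.777 at 27 per arm.

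**Step 5: one-sided alternative.** At one-sided .05, 25 per arm gives 78.7% and 26 per arm gives 80.1%, so 52 in total. Inflation gives 52/0.8 = 65 (66 with equal arms); the × 1.2 shortcut gives 63 (64 with equal arms). None of these is 68. One-sided power at 27 per arm is 81.4%.

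**The case against.** The strongest objection is that the result depends on sidedness, which the protocol never states. On a one-sided 5% test, 65 or 66 randomised patients would cover 20% loss, so 68 would suffice, and power at 27 per arm would be 81.4%. On that reading the attrition statement is true. No formula or per-arm number is printed, so how 68 was obtained is an inference.

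This stands as a condition on the finding but does not overturn it. An unqualified α of .05 is conventionally two-sided, the analysis section tests for differences without a direction, and only the two-sided calculation without attrition gives exactly 68. If the planning was in fact one-sided, the protocol would be resting its sample size on a test it does not declare, and a two-sided analysis of 27 per arm would still have about 71% power.

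A second objection is that 71% is the worst case, because the text says up to 20%. That is correct: at 10% loss (68 × 0.9 = 61.2, or 30.6 per arm) two-sided power is about 77%. But 20% is the protocol's own planning value and the level it claims to cover. Since 33 per arm already falls just short of 80%, there is essentially no reserve.

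A third objection is that enrolment is closed, so only wording can change. That bears on the cost of the correction, not on whether the figure is wrong. Nor is this a detail left out by a condensed article: the inputs and the result are both printed, and the result does not follow from the inputs.

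**Conclusion.** The concern holds. For d = 0.7, two-sided α = .05 and 1:1 allocation, 68 patients give 81% power only if all are analysed. At the 20% attrition the protocol says is included, power is about 71%, and an effect of about 0.78 standard deviations is needed for 80%. Covering that attrition would have required about 85 randomised, 17 more than planned. The conclusion assumes a two-sided test, which the document supports but does not state, and takes the protocol's own effect size and attrition at face value. The actual dropout is not given, so the power achieved may lie anywhere between these figures, or lower if loss exceeds 20%.

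**What to change.** Rewrite the Sample Size paragraph to state that the test is two-sided and to show the calculation: 68 randomised (34 per arm) gives 81% power for d = 0.7 with no attrition; with 20% attrition (27 per arm) power is about 71% for d = 0.7, or 80% for d = 0.78, using an unadjusted t test at two-sided .05. Remove the phrase "accounting for up to 20% attrition" and qualify the power claim in the Discussion in the same terms. If the original calculation was one-sided, say so, and still report the two-sided figures for the planned analysis.

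An analysis adjusted for baseline blood pressure could recover some of the lost power, but how much depends on the baseline-to-follow-up correlation, which the document does not give. Replacing d by d/√(1 − r²) at 27 per arm gives about 75% power if r = 0.3 and about 83% if r = 0.5, both values assumed. It should not be presented as restoring 80% without a stated correlation.

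The cost is wording only. No further enrolment is needed, and the stated power becomes less favourable.
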